## Abstract

**Background:**

Executive functioning impairment is common in substance use disorder and is a major risk factor for poor treatment outcomes, including treatment drop-out and relapse. Cognitive remediation interventions seek to improve executive functioning and offer a promising approach to increase the efficacy of alcohol and other drug (AOD) treatments and improve long-term therapeutic outcomes. This protocol describes a study funded by the NSW Agency for Clinical Innovation that assesses the effectiveness of delivering a six-week group-based intervention of cognitive remediation in an ecologically valid sample of people attending residential AOD treatment services. We primarily aim to investigate whether cognitive remediation will be effective in improving executive functioning and treatment retention rates. We will also evaluate if cognitive remediation may reduce long-term AOD use and rates of health service utilisation, as well as improve personal goal attainment, quality of life, and client satisfaction with treatment. In addition, the study will involve an economic analysis of the cost of delivering cognitive remediation.

**Methods/design:**

The study uses a stepped wedge cluster randomised design, where randomisation will occur at the cluster level. Participants will be recruited from ten residential AOD treatment services provided by the non-government sector. The intervention will be delivered in 12 one-hour group-based sessions over a period of six weeks. All participants who are expected to receive treatment for the duration of the six-week intervention will be asked to participate in the study. The clusters of participants who are randomly assigned to the treatment condition will complete cognitive remediation in addition to treatment as usual (TAU). Primary and secondary outcome assessments will be conducted at pre-cognitive remediation/TAU phase, post-cognitive remediation/TAU phase, two-month follow-up, four-month follow-up, six-month follow-up, and eight-month follow-up intervals.

**Discussion:**

This study will provide comprehensive data on the effect of delivering a cognitive remediation intervention within residential AOD treatment services. If shown to be effective, cognitive remediation may be incorporated as an adjunctive intervention in current treatment programs.

**Trial registration:**

Australian and New Zealand Clinical Trials Register (ANZCTR): ACTRN12618001190291. Prospectively registered 17th July 2018.

## Background

Substance use disorder (SUD) is a major global health problem, which has increased notably in the last few years [1]. In Australia, a recent publication reported that one in 200 people in the general population received treatment for substance use in 2014–15, which represents a 6% increase from the previous year [2]. Although SUD is frequently described as a chronic and relapsing condition, favourable long-term outcomes are consistently associated with alcohol and other drug (AOD) treatment completion [3]. However, failure to complete treatment, or “drop-out”, is very common in both inpatient and outpatient treatment services [4, 5].

According to a systematic review of the literature, one of the major risk factors of drop-out from AOD treatment is cognitive impairment [6]. Over the last two decades, neuropsychological research has consistently shown that substance use is associated with a significant degree of impairment in cognitive functioning. Whilst specific aspects of cognitive functioning may predate and influence the initiation of AOD use [7], increased substance use results in a greater degree of impairment [8, 9]. That is, there is a strong association between the quantity and duration of AOD use and the degree of cognitive dysfunction. Cognitive deficits in individuals with SUD may be further exacerbated by the presence of common comorbidities such as traumatic brain injury and psychiatric disorders [10, 11]. Although partial recovery of cognitive impairment may occur after immediate cessation of AOD use, many cognitive deficits fail to recover following withdrawal and abstinence [12, 13]. For example, it has been estimated that approximately 50–80% of recently detoxified individuals with SUD are cognitively impaired when assessed with the Montreal Cognitive Assessment [14–17].

In individuals with SUD, the most prominent cognitive deficits are seen in executive functioning (EF) [9, 18]. EF abilities (such as working memory, planning and organisational skills, reasoning, and self-regulation) are mediated by the frontal cortex, an area of the brain that is particularly vulnerable to substance-related impairment [19]. Common AOD treatment interventions, including counselling and psychoeducation, are heavily reliant on intact EF abilities in order to identify, promote and achieve successful behavioural change [20, 21]. Thus, EF impairment significantly predicts treatment drop-out and relapse [22–24].

Given the clinical relevance of EF deficits in the SUD population, it has been proposed that evidence-based neuropsychological interventions may be particularly useful in improving treatment outcomes and facilitating recovery [25–27]. Traditionally, cognitive remediation (CR) interventions have been inspired by two main theoretical perspectives; restoration and compensation [28]. Restorative (or “bottom-up”) approaches attempt to repair impaired cognitive skills directly by using “drill and practice” exercises, and have typically been used in mental health populations [29]. On the other hand, compensatory (or “top-down”) techniques circumvent the deficit with reliance on intact cognitive skills and environmental and prosthetic supports, and are frequently employed in acquired brain injury rehabilitation [30].

In the SUD literature, the majority of existing studies have predominantly used a restorative approach to CR, generally via “drill and practice” computerised tasks [31–35]. Whilst the results of these studies suggest that “drill and practice” leads to improvement on performance-based measures of EF, whether these improvements also lead to demonstrated improvement in everyday functioning is unclear. Performance-based measures of EF show limited ecological validity and do not relate to everyday functioning as well as inventory-based measures [36, 37]. Furthermore, there is intense debate as to the precise mechanisms of “drill and practice” training and the ability of this approach to transfer trained skills into real-world improvements, most notably treatment retention and recovery [25, 38].

In comparison, meta-analytical studies and systematic reviews have shown that compensatory CR approaches have significantly stronger effects not only on global cognition, but also on real-world functioning, than programs that focus only on restorative techniques in other cognitively impaired populations [30, 39, 40]. Whilst only a limited number of studies have examined the effects of compensatory CR in the SUD population, preliminary findings are promising [41–44]. In a sample of patients with severe alcohol-related brain damage, an intensive rehabilitation program incorporating compensatory CR strategies resulted in an 85% reduction in subsequent acute admissions [44]. Two other studies have assessed the efficacy of Goal Management Training (GMT), a predominantly “top-down” CR technique, combined with mindfulness meditation [41, 43]. Results revealed that GMT not only improved performance on tasks of working memory, impulsivity, and decision making, but also on an ecologically valid measure of goal-directed behaviour, suggesting that the intervention relates to improvements in daily life activities [43]. Another recent study showed that residents in community AOD treatment who received a combination of restorative and compensatory CR showed improvement on a performance-based measure of inhibition, as well as inventory-based measures of EF, impulsivity, self-control and quality of life [42]. Overall, these initial results support the argument that a “top-down” approach to CR may translate to real-world situations because people are better able to transfer skills from the training environment into their daily lives and that teaching such strategies helps patients compensate for the effects of persistent cognitive impairments on functioning [45, 46].

A major limitation in the existing literature is that there have been no randomised trials of compensatory CR in the SUD population. Another difficulty of the literature is that studies often exclude participants with common comorbidities such as traumatic brain injury and psychiatric comorbidities. This ultimately affects the generalisability of results. In addition, many studies have relied on performance-based measures of EF rather than more ecologically valid EF measures, which have been shown to be better predictors of real-world functioning and treatment success [47]. Finally, previous SUD literature has not followed-up the long-term effects of compensatory CR, such as treatment retention and recovery. Given findings of its success in improving functional outcomes in other cognitively impaired groups, we propose that compensatory CR aimed at improving EF is likely to be a beneficial adjunctive intervention to boost AOD treatment efficacy and long-term outcomes.

### The current study

The study will aim to examine the effectiveness of adding a CR intervention to TAU on two primary outcomes, being:A self-report inventory of executive functioning; andTreatment retention

The study will also assess the impact of CR in addition to TAU on a number of secondary outcomes:AOD useHealth service utilisationFunctional goal attainmentQuality of lifeClient satisfaction with treatmentPerformance-based measures of EFEconomic analysis

The study will be conducted as a stepped wedge randomised cluster trial. Stepped wedge designs are increasingly being utilised in the evaluation of interventions within routine treatment services and are recommended where there are limited numbers of clusters [48–50]. The study is funded by the NSW Agency for Clinical Innovation.

## Methods/design

### Study setting

The research program will be conducted at ten residential treatment facilities run by non-governmental organisations in NSW, Australia. All organisations will be abstinence-based however a portion of residents may be prescribed medications or opioid substitution treatments (OST) (e.g. methadone). Limited leave from the residential facilities, close observation by staff and other residents, and random urine tests will ensure abstinence from substances while participants are enrolled in treatment programs. Services that accommodate at least 15 residents and have a minimum project duration of 10 weeks will be invited to participate in the study.

### Ethics approval and consent to participate

The Macquarie University Human Research Ethics Committee (HREC (Medical Science)) approved the research to trial (Reference Number 5201800077), which is registered with the Australian New Zealand Clinical Trials Registry (ACTRN12618001190291). All participants will provide written informed consent to a research officer prior to participating in the trial. Consent will be provided separately for access to linked healthcare data through the Centre for Health Record Linkage. Participants will also able to request to withdraw from the study at any point during their participation (data collection, intervention or both).

### Study design

The proposed study will be conducted as a prospective stepped wedge cluster randomised trial, where randomisation will occur at the cluster level. The design involves random and sequential crossover of clusters from TAU to CR until all clusters have implemented CR (Table 1). TAU was selected as the comparator condition as the CR intervention must be demonstrated to be effective above and beyond what residential AOD services are currently offering in order to be useful as an adjunct treatment. There will be four six-week phases of either TAU or CR, interspersed by two-week test phases, at each of the ten sites. The order in which the sites receive cognitive remediation will be generated by an independent statistician using computer-generated randomisation. After the initial two-week assessment phase (weeks 1–2), all clusters will undergo 6 weeks of treatment as usual (weeks 3–8). Following the second two-week assessment phase (weeks 9–10) clients at the three sites randomised to start first will receive CR for a period of 6 weeks (weeks 11–16), then this treatment will continue for the life of the study. After the next two-week test phase (weeks 17–18), another 3 sites will be randomly selected to commence CR, and so on until all services have provided CR. Six weeks after the final post-intervention phase (weeks 33–34) an additional two-week testing phase will be allocated for follow-up (weeks 41–42). CONSORT procedures will be followed including using an intention to treat analysis [51].

**Table 1 Tab1:** Progression of sites from Treatment as Usual to Cognitive Remediation In Stepped Wedge Design

	Test Phase 1	Period 1	Test Phase 2	Period 2	Test Phase 3	Period 3	Test Phase 4	Period 4	Test Phase 5	Period 5	Test Phase 6
Week	1–2	3–8	9–10	11–16	17–18	19–24	25–26	27–32	33–34	35–40	41–42
Site 1	Test Phase 1	TAU 1	Test Phase 2	Cog Rem 1	Test Phase 3	Cog Rem 2	Test Phase 4	Cog Rem 3	Test Phase 5	F/U Period	Test Phase 6
Site 2		TAU 1		Cog Rem 1		Cog Rem 2		Cog Rem 3		F/U Period	
Site 3		TAU 1		Cog Rem 1		Cog Rem 2		Cog Rem 3		F/U Period	
Site 4	Test Phase 1	TAU 1	Test Phase 2	TAU 2	Test Phase 3	Cog Rem 1	Test Phase 4	Cog Rem 2	Test Phase 5	F/U Period	Test Phase 6
Site 5		TAU 1		TAU 2		Cog Rem 1		Cog Rem 2		F/U Period	
Site 6		TAU 1		TAU 2		Cog Rem 1		Cog Rem 2		F/U Period	
Site 7	Test Phase 1	TAU 1	Test Phase 2	TAU 2	Test Phase 3	TAU 3	Test Phase 4	Cog Rem 1	Test Phase 5	F/U Period	Test Phase 6
Site 8		TAU 1		TAU 2		TAU 3		Cog Rem 1		F/U Period	
Site 9		TAU 1		TAU 2		TAU 3		Cog Rem 1		F/U Period	
Site 10		TAU 1		TAU 2		TAU 3		Cog Rem 1		F/U Period	

Note: *Cog Rem* Cognitive Remediation Phase, *TAU* Treatment-As-Usual Phase, *F/U Period* Follow Up Period

The estimated number of participants is based on prior research in NSW residential drug and Alcohol Treatment [42]. *Discharge* refers to the discharge of participants from the residential treatment service (either through completing the program or self-discharge/drop out before the completion of the program). *Attrition* refers to drop-out from the study or otherwise being non-contactable following discharge from the treatment service.Each site will start with *n* = 20 participants on average;Within a single cohort, there will be:a 40% discharge rate over each six-week TAU/CR phase plus two-week test phase;a 65% discharge rate over the following 2 months;an 80% discharge rate over the following 4 months;a 90% discharge rate over the following 6 months; anda 95% discharge rate over the following 8 months;New clients will enter a service at the same rate as other clients leave the service;If a client enters a service during a TAU/CR phase, they will delay their participation in the trial until the next test phase;Some clients will participate in more than one CR phase;All participants who have completed at least one TAU/CR phase will be eligible for follow-up testing, which will occur at test phases 3, 4, 5 and 6.If a participant has had a CR phase they are ineligible for TAU follow-up.If a participant has had more than one CR phase they will still be eligible for CR follow-upFollow-up attrition rates have been estimated to be:65% attrition at two-month follow up75% attrition at four-month follow up85% attrition at six-month follow up90% attrition at eight-month follow up

### Participants

All participants will be attending residential AOD treatment programs in NSW. It is expected that over the course of the study approximately 440 participants will be recruited, with 40% expected to drop out within the first 8 weeks. Based on figures from 2014 to 15, we anticipate that the majority of participants will be seeking treatment for the four most common principal drugs of concern; alcohol, cannabis, amphetamines and heroin [2]. All participants will provide informed written consent and will be aged 18 years or older.

### Inclusion and exclusion criteria

All participants attending the residential programs will be invited to participate in the study. Exclusion criteria will be kept to a minimum to ensure that the study can examine the effectiveness of using CR in addition to TAU within a “real world” setting. For example, traumatic brain injury and psychiatric comorbidities are common in individuals with AOD use [10, 11], therefore these factors will not be part of the exclusion criteria in order to make the sample as representative as possible. Similarly, while the residential treatment services will be abstinence-based, a portion of clients will be prescribed OST or other medication, and these participants will also be included.

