#### Time in treatment

Duration of treatment will be provided by the Alcohol and Other Drug Treatment Services National Minimum Data Set [56]. Time spent in treatment (length of stay) as a proportion of program duration will be used as a primary outcome variable.

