### Analysis plan

Baseline characteristics will be summarised using means and standard deviations or frequencies and percentages as appropriate. The primary outcome variable will be the BRIEF-A GEC score and the effect of the intervention will be estimated using a linear mixed model. The model will include the baseline BRIEF-A GEC as a covariate and a fixed effect for each time period after baseline to account for any secular trends. We will also include random effects for treatment centre, time within centre and individual within centre to account for the clustering, repeated measurements on centre and repeated measures on individuals, respectively. The main predictor of interest will be a pre−/post-intervention variable, which will measure the overall effect of the intervention. The data will be analysed according to the intent-to-treat principle, with sensitivity analysis undertaken to include all participants under an appropriate multiple imputation model for the missing data.

Two analyses are proposed to investigate the impact of CR on treatment retention, being:Direct analysis of retention (proportion of time spent in treatment relative to program duration) across TAU and CR conditions; andComparison of historical retention data (dating back 2–5 years) with retention rates following the first CR phase for each site. A 10% increase in service retention rate will be the indicator of a clinically meaningful gain.

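### The direct retention comparison mixes a cross-section of current residents, all starting in TAU, with later new admissions, and is biased under no effect until crossover assignment and enrolment phase are fixed

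*Protocol article*

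**What the plan says.** All references are to the protocol article.

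- **Who is invited.** Inclusion and exclusion criteria: "All participants attending the residential programs will be invited to participate in the study". No limit on time since admission is given. The Abstract (Methods/design) is narrower: "All participants who are expected to receive treatment for the duration of the six-week intervention will be asked to participate in the study".
- **First condition.** Study design: after test phase 1, "all clusters will undergo 6 weeks of treatment as usual (weeks 3–8"). Sites then cross to CR at test phases 2 (three sites), 3 (three) and 4 (four).
- **Flow.** The assumptions under Table 1 are "Each site will start with *n* = 20 participants on average", "a 40% discharge rate over each six-week TAU/CR phase plus two-week test phase" and "New clients will enter a service at the same rate as other clients leave the service". A client who arrives during a phase waits for the next test phase. Some residents pass from TAU to CR. Having had CR rules a person out of TAU follow-up, but nothing says to which condition their length of stay counts.
- **Outcome.** Time in treatment: "Time spent in treatment (length of stay) as a proportion of program duration will be used as a primary outcome variable".
- **Analysis.** Analysis plan: "Direct analysis of retention (proportion of time spent in treatment relative to program duration) across TAU and CR conditions". Fixed effects for time period are stated in the same section for the BRIEF-A model only.

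**The concern.** A cross-section of people in residence on one day contains too many long stayers, because the longer someone stays the more likely they are to be present. At test phase 1 all such people start in TAU. From test phase 2 onwards new participants have been in residence for about 8 weeks or less. If total stay is then compared between conditions, the groups differ in expected stay before any effect of CR.

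A second distortion runs the other way. Residents who enrol in TAU and stay long enough are carried into CR. Counting them as CR selects CR participants on having stayed.

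Retention is one of the two primary outcomes, so either distortion could hide a real benefit or create a false one.

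**Working it through.** **1. Reproduce the planned recruitment.** Ten sites × 20 = 200 at test phase 1. Each later test phase adds 40% × 20 = 8 per site, or 80. Total: 200 + 3 × 80 = 440, which matches the Participants section.

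**2. Split by condition of the first phase.**

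| Test phase | TAU | CR |
|---|---|---|
| 1 | 200 | 0 |
| 2 | 7 × 8 = 56 | 3 × 8 = 24 |
| 3 | 4 × 8 = 32 | 6 × 8 = 48 |
| 4 | 0 | 80 |
| Total | 288 | 152 |

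The test-phase-1 cross-section is 200/288 = 69% of the TAU-first group and 0% of the CR-first group.

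**3. How many TAU-first participants reach CR.** The discharge rates are read as cumulative, so 0.60, 0.35 and 0.20 remain after one, two and three cycles.

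- Test-phase-1 enrollees: 60 × 0.60 + 60 × 0.35 + 80 × 0.20 = 36 + 21 + 16 = 73 of 200.
- Later TAU-first enrollees: 24 × 0.60 + 32 × 0.35 + 32 × 0.60 = 14.4 + 11.2 + 19.2 = 44.8 of 88.
- Together about 118 of 288.

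**4. Simulation with no treatment effect.** Admissions are uniform over time. Stay = min(T, D), with T exponential and D the programme duration. Retention = stay / D, counted from admission. A person enrols at the first test phase (weeks 0, 8, 16, 24) at which they are resident. Sites cross in the proportions 3:3:4. D is assumed, since Study setting gives only a 10-week minimum. The 40% is read in two ways:

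- A: drop-out of 40% per 8 weeks, rate −ln(0.6)/8 = 0.064 per week, with completions on top.
- B: all departures together make up 40% of residents per 8 weeks. This is impossible at 16 weeks, where completions alone would be 8/16 = 50%.

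The last two columns are CR minus TAU.

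| D (weeks), reading | Mean, test phase 1 | Mean, later | By first phase | Anyone reaching CR = CR |
|---|---|---|---|---|
| 16, A | 0.833 | 0.757 | −0.044 | +0.048 |
| 26, A | 0.735 | 0.597 | −0.090 | +0.095 |
| 26, B | 0.863 | 0.756 | −0.075 | +0.078 |
| 39, A | 0.623 | 0.453 | −0.115 | +0.122 |
| 39, B | 0.672 | 0.498 | −0.121 | +0.128 |
| 52, A | 0.527 | 0.358 | −0.117 | +0.124 |
| 52, B | 0.548 | 0.372 | −0.122 | +0.128 |

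Hand check for 39 weeks, reading B: −(200/288) × (0.672 − 0.498) = −0.121.

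**5. Effect of the Abstract's restriction.** Require at least six programme weeks remaining at invitation (reading A). The first-phase gap becomes −0.013 (16 weeks), −0.067 (26), −0.102 (39) and −0.109 (52). The gap under the other rule grows, to +0.102, +0.142, +0.147 and +0.137.

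**6. Effect of adjustment (reading A, everyone invited).**

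- First-phase assignment with a fixed effect for enrolment test phase: 0.00 at every duration.
- First-phase assignment, restricted to people admitted from the start of test phase 1: 0.00 at every duration.
- Anyone reaching CR counted as CR, with the enrolment-phase effect: +0.20 to +0.31. With the restriction instead: +0.16 to +0.32.

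Adjustment or restriction therefore works only together with the first-phase rule.

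**The case against.** The strongest reply is that a journal article gives this analysis one clause, and that covariates are commonly left to the full plan. Silence on covariates alone would indeed be no finding. What stands is that the article fixes an enrolment rule, a step schedule and a contrast for a primary outcome, and that these three together are confounded with enrolment wave. Intention to treat does not cure this, because the imbalance comes from the schedule.

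A reader might go further and infer that the comparison favours TAU. The documents do not support that. It needs first-phase assignment and no period term, and neither is stated. Counting anyone who reaches CR as CR reverses the sign. Counting each participant in every phase they start gives about zero when everyone is invited.

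A reader might also infer that the long stayers are confined to TAU. They are not: about 73 of the 200 test-phase-1 residents would go on to CR.

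Nor should the bias be measured against the 10% gain in the Analysis plan. That figure is stated alongside the historical comparison, and whether it is absolute or relative is not said.

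Finally, the Abstract limits invitation to people expected to stay six weeks. If that rule governs, the bias against CR is smaller and nearly disappears for programmes of about 16 weeks, though not for longer ones.

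**Conclusion.** The concern holds in this form: as stated, the direct retention contrast is biased under no effect under either obvious way of placing each participant in one condition, and the sign depends on a rule the article does not give. The size is about 0.04 to 0.12 of programme duration against CR with first-phase assignment, and about 0.05 to 0.12 in favour of CR if anyone reaching CR counts as CR. Reading the 40% as all departures changes these figures by less than 0.02.

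The figures rest on steady-state intake, exponential drop-out, stay counted from admission and assumed programmes of 16 to 52 weeks. Drop-out concentrated early in the stay enlarges them: at 52 weeks a Weibull shape of 0.7 gives about −0.15 and +0.16. The historical retention comparison is a separate analysis and was not examined.

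**What to change.** In the Analysis plan, state for the direct retention analysis:

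- Each participant's retention is assigned to the condition of the first phase after enrolment.
- The model has a fixed effect for the enrolment test phase, parallel to the period effects in the BRIEF-A model, and a random effect for site.
- Length of stay is counted from admission.
- Residents enrolled at test phase 1 stay in the primary retention analysis. The analysis restricted to people admitted from the start of test phase 1, under the same assignment rule, is reported as a sensitivity analysis.

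Reconcile the invitation rule in the Abstract with the one in Inclusion and exclusion criteria.

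No new data are needed, provided the data set that supplies length of stay also gives admission dates. The cost is precision. The CR contrast then rests mainly on test phases 2 and 3, where both conditions enrol: about 56 v 24 and 32 v 48, or 160 of 440 participants. First-phase assignment may also dilute the effect, because some TAU-first residents later receive CR.
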